#### Randomization

Using SPSS, each single NH unit is randomized to intervention or control condition per participating municipality and matched by urban and rural, prosperous and less well-to-do status and organizational conditions.

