### Primary and secondary outcome measures

The primary outcome in the COSMOS trial is QoL as measured by quality of life in late-stage dementia (QUALID) [49] and Quality of life in Dementia (QUALIDEM) [50] (Table 1). We also use the European Quality of Life-5 Dimensions (EQ-5D) [51] in connection with Resource Utilization in Dementia-Formal Care (RUD-FOCA) [44] as one of the secondary outcomes. Other secondary outcomes are Neuropsychiatric Inventory-Nursing Home version (NPI-NH) [52], Cohen-Mansfield Agitation Inventory (CMAI) [53], Cornell Scale for Depression in Dementia (CSDD) [54], Mobilization-Observation-Behaviour-Intensity-Dementia 2 (MOBID-2) Pain Scale [55, 56], Personal Activities of Daily Living (P-ADL) [57] and Clinical Global Impression of change (CGIC) [58, 59]. We will use Actigraphy (Philips Actiwatch Spectrum) to objectively assess sleep patterns and circadian rhythm and light exposure [60, 61]. Total medication and use of psychotropic drugs in number and dose will be assessed with respect to drug-related problems and drug–drug interactions using STOPP and START criteria [43] and anticholinergic list [43]. A full description of the primary and secondary outcomes and screening instruments MMSE [41] and FAST [42] are provided in Table 1.

**Table 1 Tab1:** Instruments used as primary and secondary outcome measures

	What does the tool measure	Tool characteristics & psychometric properties
QUALID*† [49]	QoL by cognitive function, health, function, social and psychological well-being.	11 behaviours rated on a 5-point Likert scale (range 11–55). Excellent reliability, internal consistency and validity are reported. Lower score indicates higher QoL
QUALIDEM*† [50]	QoL by self-image, affect, restlessness, care and social relation, feeling at home & active.	40 items scored 0–3 in 10 subscales yielding a sum score for each subscale; care relationship (0–21), positive affect (0–18), negative affect (0–9), restless tense behaviour (0–9), positive self-image (0–9), social relations (0–18), feeling at home (0–12), having something to do (0–6), undefined items (0–9). Sufficient reliability and validity are reported

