EQ-5D*† [51, 69]	QoL by mobility, self-care, activities, pain/discomfort and anxiety/depression, and impression of health	Patient or care-giver indicates patient`s state in f the 5 dimensions, according to 3 levels: no, some or extreme problems, and total impression of health (0–100). Scarce evidence for use in NH setting & with/in people with dementia
NPI-NH*† [52, 70]	Neuropsychiatric symptoms in dementia, caregiver distress.	Total and subscale scores are provided based on frequency & severity of symptoms (range 0–144). Good validity and reliability of the Norwegian version of the NPI-NH. Including The neuropsychiatric inventory caregiver distress scale
CMAI*† [53, X7]	Agitation & behavioural disturbances	29 items (range 29–203). Good validity & reliability
CSDD*† [54]	Depression in people with dementia	19 items rated from 0=no symptom to 2=severe. ≥8 = depression, >12=moderate-severe depression. Satisfactory inter-rater reliability and validity
MOBID-2 Pain Scale*† [55]	Two-part pain location and intensity in people with advanced dementia.	Pain intensity inferred by the patient’s pain behaviours during standardized, guided movements (Part 1), and pain behaviours related to internal organs, head and skin (Part 2). Excellent reliability, validity and good responsiveness
MMSE † [71]	Differentiation of severity of cognitive impairment	30-point scale where 0 to 11=severe impairment, 12 to 17=moderate, 18 to 23=mild, 24 to 30=no impairment
FAST*† [42, X14]	Severity of dementia	Stages dementia in 7 stages, 1 normal, 2 normal ageing, 3 possible dementia, 4 mild, 5 moderate, 6 and 7 severe dementia. Good reliability and validity
ADL*† [57]	Physical function by rating activities; feeding, moving, toilet and dressing.	The scale includes 6 items (range 0–30) Lower values indicates better functioning and independence
CGIC* [72]	Perceived improvement and efficacy	7-point rating ranging from very much worse (0) to very much improved (6). Not intended as a sensitive measure of small changes, but for changes considered clinically significant.
RUD-FOCA* [44]	Cost-analysis of time use during 24 hours	Total time per 24 hours is summed and mean time is calculated by records of required care. Validated for use in NHs, acceptable test-retest reliability and construct validity

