### Data management and analyses

A data manager will be responsible for punching, validating and merging trial data. Data will be stored on approved servers at the University of Bergen (UoB). Demographic and clinical characteristics between intervention and control at baseline will be compared using Pearson *χ*^2^ test statistics for categorical variables and independent samples *t* test for normal variables (age, diagnoses and pain diagnoses). Analysis of covariance (ANCOVA) estimates the mean effect in each trial arm, weighted across clusters (1 cluster = 1 NH unit) according to number of patients within each cluster, and from this, the mean treatment effect is estimated at each time point [47]. The intraclass correlation coefficient (ICC) expresses the proportion of the total variance in data between included clusters. Primary efficacy population includes all patients with at least one post-baseline assessment (month 4 measure), and we will use a linear intercept mixed model in a two-way repeated measures configuration to assess change over time. Treatment effect will be expressed as estimated effect of intervention, along with a 95 % confidence interval and *p* values ≤0.05 for each time point. The Mann-Whitney *U* test will be used for non-normal distributed continuous variables such as QUALID [49], QUALIDEM [50], NPI-NH [52], CMAI [53], CSDD [54], MMSE [41], MOBID-2 Pain Scale [55], CGIC [59] and P-ADL [57]. Cost-utility analysis will be performed including costs for pharmaceuticals, resource use in NHs and use of external heath care facilities [44]. A full statistical analysis plan, including potential missing data imputation for each outcome measure, will be developed through the course of the study.

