### Sample size analyses

QoL is our primary outcome measure, and ongoing comparable intervention studies conduct similar sample size analyses; however, we are not aware of large-scale studies presenting the effect of a multicomponent intervention on QoL outcome measures such as QUALIDEM or DEMQOL. Based upon the magnitude of improvement in our previous RCT on pharmacological interventions [15] for neuropsychiatric symptoms in NH patients, we estimated that a 25 % reduction of the NPI-NH scale (SD 5 standardized effect size [SES] 0.4) for comparison of the intervention and control group at month 4. To measure a difference of this magnitude requires a minimum of 81 patients allocated to each arm of the trial, for a significance level of 5 % (two sided), a power of 80 % and equal allocation. As cluster designs lead to loss of power [47], the sample size should be multiplied by 1 + (*m* − 1)*ρ*, called the design effect, where *m* is the average cluster size and *ρ* = s2b/(s2b + s2w) is the ICC, where s2b is the variance between clusters, and s2w is the variance within clusters. Based on additional assumption of an estimated ICC of 0.157 in the earlier trial with an intervention over 8 weeks [15], an average of 10 eligible patients in each cluster gives a DE = [(1 + (11 − 1) × 0.157)] = 2.57 [15]. Thus, we need a minimum of 208 (2.57 × 81) patients per arm, or 416 patients in total. We expect a drop-out rate between 20 to 25 % [64] from baseline to month 4. Thus, we need a recruitment of an additional 104 participants (520 in total), with 32 clusters (NH units) in each arm. COSMOS will be conducted in at least 64 NH units (clusters), with an average of 8–12 patients on each unit.

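### The Mann-Whitney U test is named for both primary scales without any allowance for the randomised nursing home units; if used to compare arms, its p values are not valid

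*Protocol article*

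**What the plan says.** All references are to the protocol article.

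- **Primary outcome** (Primary and secondary outcome measures): "The primary outcome in the COSMOS trial is QoL as measured by quality of life in late-stage dementia (QUALID" and, jointly, by QUALIDEM.
- **Randomisation** (Randomization): "each single NH unit is randomized to intervention or control condition per participating municipality and matched by urban and rural", together with economic status and organisational conditions.
- **Clustering in the design** (Sample size analyses): "As cluster designs lead to loss of power [47], the sample size should be multiplied by" the design effect. The ICC is 0.157, taken from an earlier 8-week trial.
- **Analysis** (Data management and analyses): three procedures reach the same scales. The ANCOVA "estimates the mean effect in each trial arm, weighted across clusters (1 cluster = 1 NH unit") according to unit size and gives a treatment effect at each time point. For repeated measurements, "we will use a linear intercept mixed model in a two-way repeated measures configuration to assess change over time". After the sentence on how the treatment effect will be reported comes the Mann-Whitney U test, which "will be used for non-normal distributed continuous variables such as QUALID [49], QUALIDEM [50], NPI-NH [52], CMAI [53"], and for CSDD, MMSE, MOBID-2, CGIC and P-ADL.

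The section does not say whether the Mann-Whitney test serves baseline comparison or the treatment effect, and it attaches no adjustment for units to it. It closes by announcing a full statistical analysis plan.

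**The concern.** A rank test protects against non-normal scores. It does not protect against dependence between patients who live in the same unit and receive the intervention together. The standard Mann-Whitney test takes every patient as an independent observation. With units randomised and a positive ICC, it understates the variance of the arm comparison, and its p value is too small on average.

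The article therefore enlarges the sample to pay for clustering and then names, for its two primary scales and most of its rating-scale outcomes, a test that ignores clustering. This is a method that the article states, not a detail that it leaves out. If it stood unchanged, an invalid p value for quality of life could be reported as prespecified.

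**Working it through.** **Inputs**

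- Two-sided significance level 5% and ICC 0.157 (Sample size analyses).
- Enrolled: 571 patients in 67 units (Abstract; Methods and design), so 571/67 = 8.52 per unit.
- Expected drop-out to month 4: 20-25% (Sample size analyses), so 8.52 × 0.80 = 6.82 and 8.52 × 0.75 = 6.39 per unit.
- Planned size: 10 per unit in the text, 11 in the printed formula, and a stated range of 8-12.

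**The plan's own figures**

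Design effect DE = 1 + (m − 1) × ICC = 1 + (11 − 1) × 0.157 = 2.57, and 2.57 × 81 = 208 per arm. Both reproduce. With m = 10, as the text has it, DE = 1 + 9 × 0.157 = 2.41. The 81 plays no part in what follows.

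**Real error of a patient-level test**

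Ignoring units understates the variance by the factor DE, so the real two-sided error of a nominal 5% test is 2 × [1 − Φ(1.96/√DE)].

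| Patients per unit | DE at ICC 0.157 | Real error |
|---|---|---|
| 6.39 (25% drop-out) | 1.85 | 14.9% |
| 6.82 (20% drop-out) | 1.91 | 15.7% |
| 8.52 (571/67) | 2.18 | 18.4% |
| 10 | 2.41 | 20.7% |
| 11 | 2.57 | 22.1% |

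**Check by simulation**

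The formula is for a comparison of means, so patient-level Mann-Whitney tests were simulated with no treatment effect (64 units, 4,000 runs per setting, normal and skewed scores). The rejection rates were 13.7-13.9% at m = 6, 15.2-16.3% at m = 7, 18.6% at m = 9, 19.1-20.2% at m = 10 and 21.4% at m = 11. They lie close to the formula. Skewness makes no material difference.

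**Sensitivity to the ICC**

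No ICC is given for QUALID or QUALIDEM, so other values are assumptions. For m from 6 to 12:

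| Assumed ICC | Real error |
|---|---|
| 0.02 | 6-8% |
| 0.05 | 8-12% |
| 0.10 | 11-18% |
| 0.20 | 17-27% |

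**Sensitivity to matching**

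If matching removed half of the between-unit variance (an assumption; the article gives no figure), the simulated error at ICC 0.157 is 9.0% at m = 6 and 11.0% at m = 9.

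**Which role does the sentence give the test?**

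- *For outcome testing:* it follows the treatment-effect sentence and is separated from the baseline comparisons by the ANCOVA, ICC and mixed-model sentences. Its list includes CGIC, which Table 1 describes as a "7-point rating ranging from very much worse (0) to very much improved (6"). Such a rating has no natural baseline value.
- *For baseline comparison:* the section opens with a chi-square test for categorical and a t test for normal variables, and a rank test for non-normal variables would complete that set. The list also includes MMSE, which the outcomes section treats as a screening instrument.

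**The case against.** The strongest reply is that the article assigns the treatment effect elsewhere. The ANCOVA is "weighted across clusters (1 cluster = 1 NH unit) according to number of patients within each cluster" and yields the effect at each time point, the mixed model handles change over time, and results are to be given as an estimate with a 95% confidence interval. A bare Mann-Whitney test gives no such estimate, which may itself suggest that it was meant for baseline tables. The section on effectiveness measures says outcome data are collected at baseline and months 4 and 9 without exempting CGIC, so one entry in a loosely written list does not prove intent. This stands to the extent that the role of the test is open.

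A reader might infer four stronger things, none of which the document supports:

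- *That the sentence can only mean outcome testing, or that the Mann-Whitney p value decides the trial.* The evidence on its role points both ways, and no sentence makes this p value decisive.
- *That false positives will run at 15-22%.* The range depends on the test being used for treatment effects and on a borrowed ICC. Its upper end needs 10-11 patients per unit, whereas enrolment gives 8.5 before drop-out.
- *That nearly every outcome is affected.* EQ-5D, RUD-FOCA, actigraphy, medication use, hospital admission and mortality are not on the list.
- *That the missing order among the three procedures, or the unstated level of the random intercept, is an error in its own right.* A statistical analysis plan commonly settles both, and one is announced. Nor does anything show the cluster-weighted ANCOVA to be unsound.

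The announced plan does not answer the core point. An unadjusted patient-level test is already named for the primary scales.

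**Conclusion.** The point holds in conditional form. A patient-level Mann-Whitney test is not valid for comparing arms in this trial, and the article names it for both primary scales and most rating-scale outcomes. Outcome testing is the likelier reading; baseline comparison remains possible.

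If it is used for treatment effects at ICC 0.157, the real error of a nominal 5% test is about 15-16% at the expected month-4 size, 18% at enrolled size and 21-22% at the planned 10-11 per unit. These figures assume equal unit sizes and no gain from matching. A smaller ICC or effective matching brings the error down, to about 8-12% at ICC 0.05. A larger ICC raises it. The direction of the error does not depend on the exact ICC as long as it is positive and matching does not absorb the between-unit variation.

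**What to change.** Remove the Mann-Whitney test from every between-arm treatment comparison, or state explicitly that it serves only to describe baseline.

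For QUALID and QUALIDEM, base inference on the mixed model that is already planned, with an explicit random effect for nursing home unit as well as for patient. If scores are skewed, use a transformation, a cluster bootstrap, or a rank test permuted at unit level in a way that respects the matching. The cluster-weighted ANCOVA need not be changed on account of this point.

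The cost is a change of wording and a small amount of analysis work. Confidence intervals will be wider than under an analysis that ignores units, but the sample size was inflated for that purpose. No new data are needed.

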### Sample size analyses

QoL is our primary outcome measure, and ongoing comparable intervention studies conduct similar sample size analyses; however, we are not aware of large-scale studies presenting the effect of a multicomponent intervention on QoL outcome measures such as QUALIDEM or DEMQOL. Based upon the magnitude of improvement in our previous RCT on pharmacological interventions [15] for neuropsychiatric symptoms in NH patients, we estimated that a 25 % reduction of the NPI-NH scale (SD 5 standardized effect size [SES] 0.4) for comparison of the intervention and control group at month 4. To measure a difference of this magnitude requires a minimum of 81 patients allocated to each arm of the trial, for a significance level of 5 % (two sided), a power of 80 % and equal allocation. As cluster designs lead to loss of power [47], the sample size should be multiplied by 1 + (*m* − 1)*ρ*, called the design effect, where *m* is the average cluster size and *ρ* = s2b/(s2b + s2w) is the ICC, where s2b is the variance between clusters, and s2w is the variance within clusters. Based on additional assumption of an estimated ICC of 0.157 in the earlier trial with an intervention over 8 weeks [15], an average of 10 eligible patients in each cluster gives a DE = [(1 + (11 − 1) × 0.157)] = 2.57 [15]. Thus, we need a minimum of 208 (2.57 × 81) patients per arm, or 416 patients in total. We expect a drop-out rate between 20 to 25 % [64] from baseline to month 4. Thus, we need a recruitment of an additional 104 participants (520 in total), with 32 clusters (NH units) in each arm. COSMOS will be conducted in at least 64 NH units (clusters), with an average of 8–12 patients on each unit.

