### Rationale for the present trial

The number of cluster randomized clinical trials (RCT) including NH patients with and without dementia that are designed to investigate the efficacy of competence improvement programs combined with clinical treatment methods has increased in the last decade. For instance, implementation of introductory communication in the form of advance care planning (ACP) in NHs resulted in fewer deaths in hospitals and reduced resource use [12], better end-of-life care and pertinent ethical discussions, and satisfied relatives and staff [14]. Another example is the stepwise protocol of treating pain (SPTP) in people with dementia which succeeded in the reduction of agitation [15], mood syndrome [16] and pain [10]. Previously, systematic medication reviews, including staff education, workshops and face-to-face interaction between the prescribing physician and an expert-group, have been found to reduce unnecessary and harmful drug prescription [17]. Finally, a current systematic review by Testad et al. (2014) highlighted the benefit of systematic organization of activities [13] and described improvements in neuropsychiatric symptoms for reminiscence therapy [18–20], personalized pleasant activities [21–23] and person-centered care [24–26].

It is of key importance that these single interventions improved either behaviour such as agitation and aggression, reduced use of the total medication and antipsychotics, or hospital admissions. However, none of the single interventions resulted in an improvement of the QoL in NH patients. In addition, the evaluation of the actual implementation process of the interventions has largely been neglected.

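### The only power calculation is for NPI-NH, a secondary outcome, so the stated 80% power does not cover the primary quality-of-life question

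*Protocol article*

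**What the plan says.** In the protocol article, Primary and secondary outcome measures states: "The primary outcome in the COSMOS trial is QoL as measured by quality of life in late-stage dementia (QUALID") together with QUALIDEM. The same section places the scale used for planning lower down: "Other secondary outcomes are Neuropsychiatric Inventory-Nursing Home version (NPI-NH"), followed by agitation, depression, pain and others.

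Sample size analyses opens by naming quality of life as primary. It then explains the switch of outcome: "we are not aware of large-scale studies presenting the effect of a multicomponent intervention on QoL outcome measures such as QUALIDEM or DEMQOL". The planning value follows: "Based upon the magnitude of improvement in our previous RCT on pharmacological interventions" for neuropsychiatric symptoms, the authors assume a 25% "reduction of the NPI-NH scale (SD 5 standardized effect size [SES] 0.4) for comparison of the intervention and control group at month 4". This, they say, "requires a minimum of 81 patients allocated to each arm of the trial", given 80% power, a two-sided 5% test and arms of equal size. The ICC of 0.157 comes from the same earlier trial, which had an 8-week intervention. The design effect of 2.57 raises 81 to 208 per arm (416 in total), and drop-out raises that to 520. No effect size, SD or ICC is given for QUALID or QUALIDEM.

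**The concern.** A power statement belongs to one outcome, with that outcome's effect, SD and clustering. Here all three are tied to NPI-NH or to the earlier neuropsychiatric trial, while the trial's main conclusion will rest on quality of life. A reader who meets 80% power in a section that begins with quality of life may take the figure to apply there.

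The stake is how a null primary result is read. If QUALID and QUALIDEM show no difference, the natural reading is that an adequately powered trial found no effect. The article gives no basis for that reading, because it never says what quality-of-life difference the trial could detect.

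**Working it through.** **1. The plan's own figure.** Inputs from Sample size analyses: standardized effect (SES) 0.4, two-sided 5%, 80% power, equal arms.

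- n per arm = 2(1.960 + 0.842)² / 0.4² = 98.1, so 99. The article says 81.
- Power with 81 per arm: 0.4 × √(81/2) = 2.546; Φ(2.546 − 1.960) = 72%.
- Effect for which 81 per arm gives 80%: 2.802 × √(2/81) = 0.44.
- The later steps follow from 81: 1 + (11 − 1) × 0.157 = 2.57; 2.57 × 81 = 208; 2 × 208 = 416; 416/0.80 = 520.

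So 80% power at SES 0.4 is not reached by this calculation even for NPI-NH.

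**2. Which inputs concern the primary outcome.**

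| Input | Value | Source | Given for QUALID or QUALIDEM? |
|---|---|---|---|
| Effect | 25%, SES 0.4 | NPI-NH, from the earlier trial | No |
| SD | 5 | NPI-NH | No |
| ICC | 0.157 | Earlier trial | No |

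**3. What the enrolled trial could detect on any scale, in SD units.** From the documents: 571 patients, 67 units, 20-25% drop-out. Assumptions: the quality-of-life ICC (0.157 borrowed, others for range), the true effect, roughly equal arms, and an unadjusted month 4 comparison with 67 − 2 = 65 degrees of freedom.

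- Analysed: 571 × 0.80 = 457 to 571 × 0.75 = 428; take 442, or 221 per arm.
- Analysed cluster size: 442/67 = 6.60.
- Design effect: 1 + 5.60 × 0.157 = 1.88.
- SE in SD units: √(2 × 1.88/221) = 0.130.
- Smallest SES with 80% power: (1.997 + 0.847) × 0.130 = 0.37. It stays 0.37 at both 457 and 428 analysed.
- Power = P(T₆₅ < SES/SE − 1.997): about 86% at 0.4, 62% at 0.3 and 32% at 0.2.

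Varying the assumed ICC with 442 analysed:

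| ICC | Smallest SES at 80% power | Power at SES 0.4 |
|---|---|---|
| 0.05 | 0.31 | 96% |
| 0.10 | 0.34 | 91% |
| 0.157 | 0.37 | 86% |
| 0.20 | 0.39 | 81% |
| 0.25 | 0.42 | 76% |

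The detectable difference in points is SES × SD. The article gives no SD for either primary scale, so this cannot be expressed on the QUALID range of 11 to 55.

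**4. Effect of baseline adjustment.** Data management and analyses plans ANCOVA and a mixed model. With an assumed baseline correlation of 0.5 and simple variance scaling, 0.37 × √(1 − 0.5²) = 0.32.

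**The case against.** The strongest reply is that nothing is hidden. Sample size analyses names quality of life as primary, says why no planning value was available for it, and says the figure used is for NPI-NH. A careful reader can see what the 80% refers to. That disclosure stands, and it explains the choice of a stand-in outcome. It does not supply a quality-of-life effect, SD or ICC. A detectable difference could be stated without any effect data, since it needs only SD, ICC and sample size.

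Two stronger readings are tempting, and neither is supported.

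- A reader might infer that the trial is underpowered for quality of life. The enrolled size argues against assuming so: at SES 0.4, power is above 80% until the ICC passes about 0.2, and baseline adjustment would improve on these figures. The 62% and 32% rest on effects of 0.3 and 0.2 that the article does not supply.
- A reader might infer that the plan contradicts its own background, because Rationale for the present trial says "none of the single interventions resulted in an improvement of the QoL in NH patients". No sentence carries SES 0.4 over to the quality-of-life scales. That remark also concerns single interventions, and the Discussion argues that a combined intervention can exceed the sum of its parts. The remark motivates the trial and is not evidence against its effect.

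It is also fair to say that the sample size can hardly change now, since Trial status reports participants already included, and that 95% confidence intervals are already planned. Both limit the consequence. Neither provides the yardstick against which an interval would be read.

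**Conclusion.** The point holds in a limited form. The article's only power calculation is for a secondary outcome, with effect basis and ICC from an earlier neuropsychiatric trial, so its 80% does not cover the primary question. Power for QUALID and QUALIDEM is unstated; it is not shown to be low. For the enrolled trial the smallest SES detectable with 80% power is about 0.37 at ICC 0.157, and 0.31 to 0.42 for ICC 0.05 to 0.25. These figures assume 20-25% drop-out, an unadjusted month 4 comparison and a borrowed or assumed ICC. The 80% is also wrong on its own terms: 81 per arm gives about 72% at SES 0.4. The matter should be put right, but it does not call the design into question.

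**What to change.** 1. State that the calculation was made for NPI-NH, and correct it: at SES 0.4, 81 per arm gives about 72% power, and 80% needs 99 per arm before the design effect. Simply relabelling the 80% as NPI-NH power would repeat a wrong figure.
2. Before month 4 results are known, state the detectable difference in scale points on QUALID and on QUALIDEM for 571 patients in 67 units. Take the SD and unit ICC from baseline data pooled over both arms, which needs no comparison between arms. Show the result over a range of ICC, because a baseline ICC is only a proxy for the baseline-adjusted ICC at month 4. The statistical analysis plan that the article says is still to be developed is the natural place.
3. Commit to judging a null quality-of-life result by its 95% confidence interval against that difference, not by the 80% power claim.

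The cost is a short calculation on data already being collected, some wording, and a less favourable stated power figure. No extra patients are needed.

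### The sample-size paragraph's inputs do not agree with its figures: SES 0.4 gives 99 per arm, not 81; the design effect uses 11 for a stated 10; and 520 covers only 20% drop-out

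*Protocol article*

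**What the plan says.** Everything is in one paragraph of the Protocol article, under Sample size analyses. The target is a reduction on NPI-NH at month 4, with SD 5 and "standardized effect size [SES] 0.4". The calculation is set "for a significance level of 5 % (two sided), a power of 80 % and equal allocation". On that basis the article says the comparison "requires a minimum of 81 patients allocated to each arm of the trial".

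The number is then inflated for clustering by 1 + (m − 1)ρ, where m "is the average cluster size" and ρ is the intraclass correlation, taken as "an estimated ICC of 0.157 in the earlier trial". The text states that "an average of 10 eligible patients in each cluster gives a DE" of 2.57, but the bracket that follows contains 11 − 1. This leads to 208 per arm and 416 in total.

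Drop-out to month 4 is expected to be 20 to 25%. The article concludes that "we need a recruitment of an additional 104 participants (520 in total"), with 32 units in each arm, and that "COSMOS will be conducted in at least 64 NH units (clusters"), averaging 8 to 12 patients per unit. Methods and design reports 571 participants in 67 units.

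**The concern.** Three links fail against the paragraph's own inputs: the step from the effect size to 81, the cluster size put into the design effect, and the allowance for drop-out. The first and third make the requirement too small; the second makes it too large.

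This paragraph is the published justification for the size of the trial, and the Discussion refers back to it when it says that enough patients and clusters were included. As printed, a reader cannot tell whether 80% power refers to an SES of 0.40 or 0.44, or which cluster size it assumes. That matters most if the result is null and readers ask what difference the trial could have detected.

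**Working it through.** **Inputs, all from the Protocol article.** SES 0.4; two-sided α 0.05; power 0.80; 1:1 allocation; ICC 0.157; average cluster size stated as 10 and inserted as 11; drop-out 20–25%; target 520 in 64 units; included 571 in 67 units.

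**Reproducing the plan from 81 onward.** 1 + (11 − 1) × 0.157 = 2.57. 2.57 × 81 = 208.2, given as 208. 2 × 208 = 416. 416/0.80 = 520, which is 104 more. These steps are correct as calculated.

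**Link 1, SES to n per arm.** n = 2(z₀.₉₇₅ + z₀.₈₀)²/SES² = 2 × (1.960 + 0.842)²/SES² = 15.70/SES².
- SES 0.40: 15.70/0.16 = 98.1, so 99 per arm (99.1, so 100, with the t distribution).
- SES 0.44: 15.70/0.1936 = 81.1, which is the printed 81 apart from rounding up.
- Power of 81 per arm at SES 0.40: Φ(0.40 × √(81/2) − 1.960) = Φ(0.586) = 72%.
- A one-sided 5% test gives 78, so that does not explain 81. A baseline correlation of about 0.42 would, but none is stated.

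**Link 2, design effect (DE).**
- m = 10, as stated: 1 + 9 × 0.157 = 2.413.
- m = 11, as inserted: 2.57.
- m = 520/64 = 8.125, as the recruitment target implies: 1 + 7.125 × 0.157 = 2.119.

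At 81 per arm, m = 10 gives 195.5, so 196 per arm against the plan's 208. The use of 11 is therefore conservative.

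**Link 3, drop-out.** 520 × 0.80 = 416, but 520 × 0.75 = 390. Keeping 416 at 25% needs 416/0.75 = 554.7, so 555. The figure 520 also equals 416 × 1.25, which adds 25% to the analysed number but allows for a loss of only 20%.

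**Effect on power.** Effective n per arm = N/(2 × DE); power = Φ(SES × √(n/2) − 1.960), a normal approximation throughout.

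| DE (m) | SES | 416 analysed | 390 analysed |
|---|---|---|---|
| 2.57 (11) | 0.40 | 72% | 69% |
| 2.41 (10) | 0.40 | 75% | 72% |
| 2.12 (8.1) | 0.40 | 80% | 77% |
| 2.57 (11) | 0.44 | 80% | 77% |

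**The sample actually included.** 571/67 = 8.52 per unit, so DE = 1 + 7.52 × 0.157 = 2.18. Drop-out of 25% and 20% leaves 428 and 457. At SES 0.40:
- With DE 2.18: 80–83% by normal approximation (79–81% by t with 65 degrees of freedom, the number of units minus 2).
- With the DE at the analysed cluster size (428/67 = 6.4, DE 1.85; 457/67 = 6.8, DE 1.91): 86–87% by normal approximation (85–86% by t).

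**The case against.** The strongest reply is that 81 may be right and 0.4 merely rounded. An SES of 0.44 prints as 0.4 to one decimal and reproduces 81; with 416 analysed and DE 2.57 it also returns the stated 80%. This reading is plausible and should be offered to the sponsor, but the article does not state 0.44. On either reading the printed effect size and the printed n cannot both stand.

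It can also be said that the slip from 10 to 11 errs on the safe side, that 8.1, 10 and 11 all lie within the stated 8 to 12 per unit, and that 571 patients were included, so that 428 remain even at 25% loss. Loss would have to exceed 1 − 416/571 = 27% before fewer than 416 remained. All of this stands. It limits the practical consequence but does not make the paragraph consistent.

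Finally, the calculation concerns NPI-NH, which the article lists as a secondary outcome, so correcting it will not show what the trial can detect on QUALID or QUALIDEM. That is true, but it is a separate matter.

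A reader might go further and infer that the trial is underpowered, citing 69–75% power. The documents do not support this. Those figures require an SES of exactly 0.40 together with a cluster size of 10 or 11, whereas the target of 520 in 64 units implies 8.1. Nor does the whole chain fail: every multiplication after 81 is correct.

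**Conclusion.** The point holds as an inconsistency between inputs and figures in one paragraph. At the stated SES of 0.40 the unclustered requirement is 99 per arm, 22% more than 81 (99/81 = 1.22). The design effect uses 11 for a stated 10, and 520 meets the minimum of 416 only at the lower drop-out bound, falling 26 short (416 − 390) at the upper.

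The discrepancies partly cancel. At SES 0.40, 416 analysed patients have between 72% and 80% power according to which of the paragraph's cluster sizes is used, and the included sample has about 80% or more by normal approximation. What is damaged is the stated justification.

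The power figures assume ICC 0.157, equal allocation, equal cluster sizes and a simple comparison of means inflated by the design effect, with no gain from baseline adjustment. That SES 0.40 does not give 81 depends on none of the clustering assumptions.

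**What to change.** Restate the paragraph with one set of inputs:
- Either SES 0.40 with 99 per arm, or SES 0.44 with 81 per arm, whichever was intended.
- One planned average cluster size, given in the text and used in the design effect.
- Recruitment shown for both 20% and 25% drop-out.

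For example, with m = 10, SES 0.40 gives 99 × 2.413 = 238.9, so 239 per arm, 478 in total, and 598 to 638 recruited. With m = 10, 81 per arm gives 196 per arm, 392 in total, and 490 to 523 recruited.

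The achieved 8.5 per unit should not be put into the planning requirement, since that would fit the justification to the enrolment. Instead, report separately, by one named method, the power of the 571 patients in 67 units, and say whether the design effect uses the recruited or the analysed cluster size. At SES 0.40 and ICC 0.157 this is about 80–83% (normal) or 79–81% (t) with DE 2.18, and about 86–87% or 85–86% with the analysed cluster size.

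The cost is one corrected paragraph and no further recruitment. The downside is a slightly less favourable statement: a larger requirement if 0.40 was meant, or a larger detectable effect if 0.44 was. If 0.40 and m = 10 are kept, the restated target will exceed 571; the separate power statement explains why the smaller units offset this.
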